### Consortium of Experts Involved in the Study

The study is supervised by several experts in Germany, Switzerland, and Austria (Figure 2). Each country provides the logistics, manpower, and experts to collect and control data collection and analysis. Interpretation of data will be supported by oncologists. Data are added to a REDCap study registry, which is provided by the Clinical Trial Unit in Bern, Switzerland, which is also responsible for statistical analysis. The data platform will be programmed by an IT company, and data presentation will be optimized by the involved experts and by the patients’ representatives. The data platform, called “FertiTOX,” will be part of the network “FertiPROTEKT.”

**Figure 2 figure2:**
[figure not shown]
The consortium of experts who control the project.

### The FertiTOX Platform

The FertiTOX platform is an internet-based information platform that will be accessible to everybody and will be structured on the basis of the *ICD* cancer disease groups (Figure 3). The brand name FertiTOX has been registered and the domains will be used. A study website [20] has been set up.

Data of women and men will be presented on the FertiTOX platform in 3 hierarchies:

First hierarchy: presentation of data regarding incidences and 5-year survival according to the *ICD-*classified cancer disease.Second hierarchy: presentation of already published data regarding gonadotoxicity and fertility preservation issues regarding specific *ICD-*classified diseases.Third hierarchy: presentation of prospective short-term and long-term data on the ovarian reserve and sperm quality before and after gonadotoxic therapies in accordance with *ICD-*classified diseases.

Once the internet-based platform is successfully established, a platform-specific app will be developed to allow easy retrieval of data.

**Figure 3 figure3:**
[figure not shown]
The internet-based platform FertiTOX that will be used to distribute the data. *ICD: International Classification of Diseases*.

### Dissemination

Data about the progress of the study will be disseminated through a study website [20]. The findings will be propagated through journal articles, conference presentations, and the FertiTOX platform.

### Ethical Considerations

Ethical approval has been granted by the relevant ethics committees. In Switzerland, all 7 cantonal ethical committees have provided consent for all 21 participating centers. In Germany, the ethics committee in Heidelberg and in Austria, the committee in Innsbruck were chosen as the national leading ethical committees. Based on the ethical votes approved by these 2 committees, all other participating centers in Germany and Austria submitted an ethics application to their ethical committee.

Written consent was obtained from the participants. The participants have been informed about the processing of data and their rights. The participants also provided written consent for anonymized data to be transferred to other registries for further analysis if the other registries have the same high security standards as the REDCap registry. The data are collected in a REDCap study registry that complies with several data security and confidentiality conditions. Specific identifiers are not added to the registry; only the year of birth is added. The data are stored in Bern, Switzerland.

The participating centers can only access the patient’s data that they have added to the registry. The patients can be identified with an individual code generated by the REDCap system, which is locked in a safe place by the investigator of the participating center. Traceability of the data is ensured by these identification codes. Patients provide permission to be followed up. Patients are only contacted by the center or by authorized personnel employed by the principal investigator or the national representatives of the study. Statistical analysis will be based on anonymized data.

No compensation will be offered to the patients (potential users of the internet-based platform) for participating in the study.

## Results

As of February 18, 2024, the following has been accomplished.

The first systematic review analyzing the impact of cancer therapies on bone tumors has been accepted for publication (in the *Journal of Adolescent and Young Adult Oncology*). Nine more systematic reviews have been initiated, encompassing the impact of cancer therapies on fertility in testicular cancer; soft tissue cancer; breast cancer; eye, brain, or central nervous system cancer; Hodgkin lymphoma; non-Hodgkin lymphoma; rectal or sigmoid cancer; leukemia; and on bone marrow transplantation.

The prospective cohort study has been prepared. All Swiss ethics committees and the leading ethics committees in Germany and in Austria have provided their approval. In total, 70 infertility centers (Multimedia Appendix 1) have started to be prepared for data collection. The study registry has been set up and activated, and a study website [20] has been created.

Funding for the study has been obtained from several funding bodies, which were not involved in the study’s conceptualization, analysis, and data dissemination.

Recruitment of the patients started on December 1, 2023, and initial data are expected to be uploaded on the FertiTOX platform in 2026.

## Discussion

### Anticipated Findings

The first systematic reviews we have already carried out have revealed that data on the impact of gonadotoxic therapies on fertility are quite comprehensive in some diseases such as breast and testicular cancers and Hodgkin lymphoma. For these diseases, a meta-analysis will also be carried out to analyze the overall effect of oncological therapies on fertility. Furthermore, for these diseases, the gonadotoxic effect of specific chemotherapy protocols on fertility will also be assessed. For the other diseases, data are very poor, and outcome parameters will probably need to be limited to a rather vague outcome parameter defined as “suspected infertility.” Long-term fertility data based on the ovarian reserve and sperm parameters and on spontaneous conceptions and conceptions using cryopreserved gametes or gonadal tissues are very poor or nonexistent in all kinds of cancers.

This finding supports the necessity to perform the large prospective cohort studies, as described in this paper. This cohort study has already successfully been set up and data collection was initiated on December 1, 2023.

Robust data on the gonadotoxicity of different treatment regimens, mainly in cancer therapies, is the last major deficit in fertility preservation. All other requirements have been established in many countries, such as fertility preservation procedures and specialized centers to counsel patients and to perform these procedures. Furthermore, many oncologists have been sensitized to address the fertility risk of cancer therapies and the possibility to perform fertility preservation procedures.

However, comprehensive data about the specific gonadotoxicity of different treatment regimens required to counsel patients and to decide if fertility preservation measures should be recommended or not are still missing.

Previous studies have addressed fertility issues in patients with cancer and the impact of cancer therapies on fertility, but these studies are mostly based on spontaneous pregnancies following cancer therapies or are based on data such as the onset of puberty, cycle regularity, and low sperm counts. Studies based on pre- and postchemotherapy levels of AMH and sperm counts are very limited and are mainly limited to female patients with breast cancer [21-24].

To bridge this data gap, we designed a study to analyze published data and data that will be collected in at least 3 countries by centers belonging to the FertiPROTEKT network. The data will be analyzed und disseminated via the FertiFOX web-based platform to provide patients, researchers, and clinicians access to the analysis, which will be graphically illustrated. By including patients’ representatives in the data analysis, we will ensure that the data are presented in a manner that is also understandable to patients. The data will not only be presented as a single curve presenting the means and showing odds ratios and CIs, which presents the average impact of therapies on gonadal function, but also show individual variations by presenting a set of curves.

The study has been designed to follow up on patients for at least 10 years. Such a long follow-up will enable us to evaluate how many patients have undergone fertility-preserving procedures but unfortunately did not survive. Furthermore, we will be able to estimate how many patients conceived spontaneously or by using the frozen gametes and gonadal tissue. Such an analysis is essential to evaluate the long-term efficacy of fertility preservation counseling and treatment. We are aware that some patients might be lost to follow-up. However, as the number of included patients is expected to be very high, it can be assumed that the amount of data will still be sufficiently high.

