### Sample Size Calculation

A power calculation was performed to determine whether the expected number of patients is sufficient to detect an effect of cancer treatment on fertility with a reasonable power.

The calculation was performed for the primary outcome (ie, sperm count for men and AMH concentration for women) for men and women separately. Calculations were performed within each cancer entity and for each specific treatment protocol separately with a paired *t* test using Stata (release 17.0; StataCorp).

We set the effect size so that a relative risk of 50% was not missed. For the sperm count, where the mean value in healthy men is 64 million (SD 47 million) [17], this would correspond to an effect size of 0.67. For AMH concentration in women, where means and SDs can be assumed to be equal [18], it would correspond to an effect size of 0.5. The intraindividual correlation was set to 0.5 [17,18]. To account for multiple testing (analysis will be performed with 43 treatment groups for men and women separately), the Šidák correction was used, and the significance level was adjusted to 0.0006 (2-sided).

Table 1 shows that a sufficient power of >80% will be reached for most treatments. If the number of cases was twice as high and the intrapatient correlation coefficient was 0.7, a power of >80% would be reached for all treatment levels. As the study is expected to be extended, a sufficient number of patients can be expected in order to reach this goal.

**Table 1 table1:** Expected number of cases and resulting power reached per specific treatment (treatment protocols) in the most common *ICD (International Classification of Diseases)* cancer groups [19].

*ICD* cancer group	Cases, n^a^	Specific treatments (treatment protocols), n	Effect size (females/ males)^b^	Power (females/ males)^b^, %/%
Breast	2000	6	0.5/—^c^	100/—
Hodgkin lymphoma	1000	2	0.5/0.68	100/100
Bone and articular cartilage	400	3	0.5/0.68	98.6/100
Female genital organs	350	3	0.5/—	96.5/—
Male genital organs	2000	4	—/0.68	—/100
Digestive organs	200	7	0.5/0.68	14.3/41.4
Mesothelial and soft tissue	200	3	0.5/0.68	67.2/96.7
Eye, brain, and central nervous system	300	2	0.5/0.68	99.5/100
Non-Hodgkin lymphoma	300	8	0.5/0.68	26.2/64.4
Leukemia	200	5	0.5/0.68	30.6/70.8

^a^The estimation of the number of cases is based on the number of patients previously counseled and documented in the FertiPROTEKT and FERTISAVE registries.

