### Data Analysis

The impact of cancer therapies and chemotherapies on the primary outcomes will be assessed for each *ICD* cancer group [19] and for each specific treatment regimen separately by comparing values measured before and after the gonadotoxic therapy using paired *t* tests. *P* values will be adjusted for multiple testing using the false discovery rate controlling procedure.

Consequences on other fertility parameters measured before and 12-15 months after the end of gonadotoxic therapy (ie, AMH, FSH, LH, and E2 concentrations in women and total testosterone, FSH, and LH concentrations and total sperm count, sperm concentration and motility in men) will be assessed using the same methodology, but without false discovery rate adjustment. Long-term consequences will be investigated later by comparing values measured before and 5 and 10 years after the gonadotoxic therapy. However, due to the long period until the final analysis, statistics might be adapted in relation to future development of cancer and fertility-preserving therapies.

As age was identified to potentially modify the effect of gonadotoxic therapy on female fertility, we will additionally conduct stratified analyses and document the impact of gonadotoxic therapy in the different female age groups.

Finally, the effects of different cancers, treatment protocols, age, and the presence of the patients’ children before cancer therapy on primary and secondary fertility outcomes will be analyzed using linear mixed effect models.

The frequency of patients undergoing fertility-preserving treatments, namely freezing of ovarian tissue, oocytes and embryos, testicular tissue, and sperm will be calculated for each *ICD* cancer group and for each specific treatment protocol separately and additionally presented with the associated 95% Wilson CI. Potential effects of the patients’ characteristics on the abovementioned binary outcomes will be analyzed using logistic regression analysis.

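### Table 1's power assumes that no patient is lost, and the Discussion's reassurance that large numbers will absorb loss does not hold for the small protocols

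*Protocol article*

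**What the plan says.** **Protocol article, Data Analysis.** The primary outcomes (AMH in women, sperm count in men) are analysed for each cancer group and each treatment regimen separately, "by comparing values measured before and after the gonadotoxic therapy using paired" *t* tests. End Points places the second measurement 12-15 months after treatment ends.

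**Protocol article, Sample Size Calculation.** Power is computed for the same test, per protocol and sex. Footnote a to Table 1 says the case estimate is "based on the number of patients previously counseled and documented in the FertiPROTEKT and FERTISAVE registries". Footnote b divides cases by the number of protocols to get patients per protocol. Neither footnote mentions a deduction for refusal, death or a missing second sample. The text says more than 80% power is reached for most treatments, and that doubling the cases with a correlation of 0.7 would bring every protocol above 80%.

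**Protocol article, Discussion (Anticipated Findings).** In a paragraph on follow-up of at least 10 years, the article says some patients will not survive and some may be lost. It then says that, because the number included should be very high, "it can be assumed that the amount of data will still be sufficiently high". This is the article's only statement on the effect of loss; the Limitations section does not mention it.

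**The concern.** A counselled patient adds to a paired *t* test only after consenting, surviving and giving a second blood or semen sample. If Table 1 counts every expected case as a pair, its power is an upper limit on this count.

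The Discussion argues from the size of the whole study, but the tests are run protocol by protocol, and several protocols are expected to have only 28 to 66 patients. A large total does not help them.

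Size also affects precision only. If patients who return differ from those who do not, for example through relapse or concern about fertility, the paired completers can misstate a regimen's effect however many there are. The results are meant for counselling patients by disease and regimen, so both matters bear on how they will be used.

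**Working it through.** **Inputs (Sample Size Calculation, Table 1 and its footnotes).**
- Two-sided alpha 0.0006. The Šidák value for 2 × 43 = 86 tests is 1 − 0.95^(1/86) = 0.000596.
- Effect size d: 0.5 for women; for men 32/47 = 0.681, printed as 0.67 in the text and 0.68 in the table.
- "The intraindividual correlation was set to 0.5".
- Pairs per protocol: n = cases / protocols, rounded down.
- Loss rates are assumed; the article gives none.

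**Formula.** The standardised paired difference is d_z = d / √(2(1 − ρ)), so d_z = d at ρ = 0.5. Power comes from the noncentral *t* distribution with n − 1 degrees of freedom and noncentrality d_z√n.

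**Step 1: reproduce Table 1 at 0% loss.** For digestive organs, 200/7 gives n = 28 and power 14.3% for women and 41.5% for men (printed 14.3/41.4). For leukemia, 200/5 = 40 gives 30.7/70.9 (printed 30.6/70.8). All ten rows match within about 0.1 point. No loss is therefore applied between the tabulated cases and the printed power.

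**Step 2: pairs needed for 80% power.** 79 women or 46 men per protocol. The table supplies 28 (digestive), 37 (non-Hodgkin) and 40 (leukemia), short for both sexes, and 66 (soft tissue), short for women. These have no reserve. To end with 79 pairs at 30% loss, 79/0.7 = 113 women must be enrolled per protocol; for 46 pairs, 46/0.7 = 66 men.

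**Step 3: apply loss, n = floor((1 − loss) × cases / protocols).** Power, women/men, %:

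| Group | Printed | 10% loss | 20% loss | 30% loss |
|---|---|---|---|---|
| Digestive | 14.3/41.4 | 11.0/33.2 | 8.1/25.1 | 6.4/20.1 |
| Non-Hodgkin | 26.2/64.4 | 20.7/54.9 | 16.8/46.9 | 12.1/35.9 |
| Leukemia | 30.6/70.8 | 24.9/62.2 | 19.3/52.3 | 14.3/41.5 |
| Soft tissue | 67.2/96.7 | 59.8/94.3 | 50.1/89.3 | 39.7/81.1 |
| Female genital | 96.5/— | 93.9/— | 89.2/— | 81.7/— |
| Bone (women) | 98.6 | 97.2 | 94.2 | 89.2 |

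Breast, Hodgkin and male genital stay at about 100% throughout. They keep 80% power until roughly 75-90% are lost.

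**Step 4: count the tests above 80%.** Of the 43 protocols, 43 − 4 = 39 apply to women and 43 − 6 − 3 = 34 to men, giving 73 tests. At 0% loss, 16 women's tests (6 + 2 + 3 + 3 + 2) and 14 men's (2 + 3 + 4 + 3 + 2) exceed 80%, so 30 of 73. At 30% loss it is still 30. At 50% loss, bone, female genital and CNS in women (3 + 3 + 2) and soft tissue in men (3) drop out: 30 − 11 = 19.

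**Step 5: the fallback.** With ρ = 0.7, d_z = 0.5/√0.6 = 0.645 for women. Doubled digestive cases give 400/7 = 57.1, so n = 57 and power 88.2% at 0% loss. At 20% loss n = 45 and power is 72.9%; at 30%, n = 40 and 63.4%. Here 80% power needs 50 pairs, so the claim fails once loss exceeds about 1 − 50/57.1 = 12.5%.

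**The case against.** **The reassurance belongs to the 10-year follow-up, not to Table 1.** True of its position: it is not offered as a defence of the power calculation. But its wording is general and the article says nothing else about the effect of loss on the 12-15 month comparison.

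**The weak protocols are already disclosed.** Also true. Table 1 prints their low power, and the text says more cases are needed and expects an extension. A reader might infer that the article hid these shortfalls, or that moderate loss makes its adequate protocols inadequate. The documents support neither: at 30% loss no test printed above 80% falls below it. What is undisclosed is that the printed powers, and the fallback offered as the remedy, presuppose complete pairs.

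**Alpha 0.0006 is not the planned analysis.** Data Analysis specifies false discovery rate control, which is less strict when many effects are real. In a simulation of the Benjamini-Hochberg procedure at an assumed 5% over 73 tests, with 30% loss and the planning effect in every test, power in women was about 54% for digestive and 66% for non-Hodgkin; with the effect in half the tests, about 41% and 54%. The figures in the working thus show what loss does to Table 1's own calculation, not the power of the final analysis. Loss still lowers power under either procedure.

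**The case numbers may already be discounted.** Footnote a says only that they derive from counselled patients, so Table 1 cannot be read as the literal number counselled. An earlier discount cannot be excluded, though none is described.

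**Handling of missing data may be in the analysis plan.** It may. That plan is not shown, so no absence of such methods can be inferred, and weighting schemes or retention displays are not asked for here. Retention measures are in fact described: contact by telephone, email or post, and reminders to centres. What stands is narrower: a printed argument that numbers alone suffice.

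**Conclusion.** The point holds in limited form. Table 1 treats every expected case as a complete before-after pair, while the article itself expects deaths and loss.

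- For breast, Hodgkin and male genital cancers the reassurance is sound as regards power.
- For digestive, non-Hodgkin and leukemia protocols in both sexes, and soft tissue in women, there is no reserve. An assumed 30% loss roughly halves power that is already below 80%.
- The count of adequately powered tests is unchanged at 30% loss and falls from 30 to 19 of 73 at 50%.
- The fallback claim fails for digestive cancers in women above about 12.5% loss.
- In no group does sample size remove bias from selective return. The article gives nothing from which to size that bias.

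These results rest on the printed case numbers, alpha 0.0006, the stated effect sizes and correlations, and assumed loss rates. They use the full cases-per-protocol number for each sex, because only that reproduces the table. Footnote b's 1:1 sex split would lower the two-sex powers further, which is a separate matter.

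**What to change.** 1. Restate Table 1 and the fallback sentence in evaluable pairs at stated retention values, for example 90%, 80%, 70% and 50%. Say whether the case numbers already allow for refusal or loss.
2. In the Discussion, limit the reassurance to the large groups, and state that a large number of patients does not remove bias when return is selective.
3. Report the linear mixed model already planned in Data Analysis as a companion to the completers-only paired *t* test. Fit it to all patients with a baseline value, with the covariates already named (cancer, protocol, age, children before therapy). It uses patients without a second value and is valid if return depends only on what the model contains; it does not protect against loss that depends on the unseen outcome.

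Cost: recalculation and wording, and a less favourable stated power. No extra patients or measurements.

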### Limitations

A limitation of this study is that data are mainly collected in Germany, Switzerland, and Austria. Accordingly, data will not be available for other treatment regimens performed elsewhere. However, as other countries are also invited to participate in this study, this limitation could possibly be reduced. Another limitation is that children will not be evaluated primarily because the study is based on AMH values and sperm parameters, which can hardly be interpreted in (AMH concentration) or cannot be collected from (sperm parameters) children.

The last limiting factor is that new therapies are evolving very fast and that new combination therapies combining conventional chemotherapy agents and immune therapies will be developed, which will increase the complexity of our data analysis. However, it is expected that this limitation can at least in part be compensated by the prospective design of the study, which will include a higher number of new therapies. Furthermore, the impact of checkpoint inhibitors, which have been shown to be gonadotoxic in female mice, will be analyzed separately in women with melanoma undergoing adjuvant therapy with checkpoint inhibitors. These results can be used to better estimate the gonadotoxicity of combination therapies involving checkpoint inhibitors.

### Conclusions

In conclusion, the study can be expected to bridge the data gap regarding the gonadotoxicity of several therapies and gonadotoxic treatment regimens to better counsel patients regarding their infertility risk and their need to undergo fertility-preserving procedures.

